##### Static balance

Static balance is assessed by a postural sway test that measures how well a person can maintain their balance during quiet standing. Increased sway indicates poor balance control, is associated with an increased risk of falls, and is greater in populations with neurologic impairment [34, 35]. Postural sway is measured with a Mobility Lab Opal sensor and software (APDM Wearable Technologies, Clario, Portland, OR). The wireless, Opal inertial sensor placed on the lumbar region captures multiple postural sway variables, including total sway area (m^2^/s^4^) and mean sway velocity (m/s). Participants are asked to stand as still as possible with feet together and hands on hips for 30 s. The test is first conducted with eyes open and then repeated with eyes closed.

##### Dynamic balance

Dynamic balance is measured by the Timed-Up-and-Go (TUG) test, a widely accepted clinical measure of dynamic balance in older adults and clinical populations [36]. The TUG test evaluates the time in seconds that it takes an individual to rise from a chair, walk 3 m at their usual pace, turn around, and return to a seated position in the chair. The procedure is repeated for a total of 2 averaged trials to calculate TUG time. Slower TUG times are associated with an increased risk of falls and disability and have been observed in taxane-treated breast cancer survivors relative to healthy controls [31, 37–39].

#### Daily mobility

Daily mobility is measured with instrumented socks with inertial sensors embedded into thin, neoprene fabric (APDM Wearable Technologies, Clario) [40–42]. For 4–7 days after each clinic assessment, participants are asked to wear the socks during waking hours for at least 6–8 h and then charge them overnight. Raw data are stored on the sensors and then uploaded to a secure server for analysis with Motion Studio software (APDM Wearable Technologies, Clario). Examples of mobility measures calculated during daily monitoring are reported in Table 1. Mobility measures are calculated with proprietary algorithms from APDM, many of which have been validated [43–45]. The measures are calculated by combining the 3 axes of linear acceleration with 3 axes of angular velocity and the magnetometer (all sampled at 128 Hz) to obtain the orientation of the limb in space. Wireless synchronization allows precise temporal binding of data across limbs. Walking bouts and turning events are first identified, followed by calculating metrics within each walking bout and turning event.

**Table 1 Tab1:** Selected mobility measures obtained by the instrumented socks

Activity	Gait Quality	Turning Quality
% of day active	Stride velocity (cm/s)	# turns/hour
# walking steps/day	Stride length (m)	Turn velocity (°/s)
# walking bouts/day	Cadence (steps/min)	Turn angle (°)
Duration of longest bout/day (s)	Double support time (ms)	Turn duration (s)
	Angle of foot at heel strike (°)	Turn angle/step (°/step)

#### Daily physical activity

Daily physical activity is measured using accelerometry, which is considered the gold standard for objective physical activity monitoring and has been used during various phases of cancer care [46]. Participants are given an ActiGraph GT9X Link watch (Actigraph, Pensacola, FL). They are asked to wear it on their non-dominant wrist for 24 h per day for 4–7 days after each clinic assessment so that objective measures of sleep can be obtained and considered in future analyses. Participants who are unwilling to wear a watch while sleeping are asked to wear the watch for at least 6–8 h per day during waking hours for 4–7 days after each clinic assessment to obtain daily activity data. Data are analyzed with ActiLife software (version 6) [47]. Of particular interest in this study are total energy expenditure (kcal/d) and time spent in sedentary, light, and moderate-vigorous activities over 7 days after each clinic assessment.

#### Patient-reported physical functioning

Perceived physical function is measured using the physical functioning subscale of the European Organization for Research and Treatment of Cancer Quality of Life Questionnaire (EORTC QLQ-C30) [48]. The physical functioning subscale of the QLQ-C30 is valid and reliable [48, 49]. Scores on this subscale range from 0–100, with higher scores indicating better functioning. This survey is administered at time points corresponding to each clinic assessment.

#### Patient-reported disability

Perceived disability is evaluated using the disability component of the Late-Life Function and Disability Instrument (LLFDI), which assesses disability in terms of frequency and limitation in performing 16 life tasks [50]. The LLFDI is a valid and reliable instrument that we have previously used to document significantly more disability in cancer survivors with CIPN than in asymptomatic survivors [4, 50]. Scores range from 0 to 100, with higher scores indicating less disability. This survey is administered at time points corresponding to each clinic assessment.

#### Quality of life

Quality of life is assessed using the EORTC QLQ-C30 [48]. Global quality of life and subdomains (physical, emotional, social, role, and cognitive functioning) are scored from 0–100, with higher scores indicating better quality of life or functioning. The individual subscales and summary scores are valid and reliable [48, 49], and good test–retest reliability and acceptable validity have been demonstrated in patients with CIPN [22]. This survey is administered at time points corresponding to each clinic assessment.

### Falls

#### Falls

Falls that occurred during the 12 months prior to enrollment are assessed retrospectively at baseline, and falls that occur prospectively are assessed at weekly intervals using in-house surveys. These surveys ask patients about the number of falls, the nature of any injurious falls, and medical care resulting from a fall during the observation period. A fall is defined as unintentionally coming to rest on the ground or at some other lower level, not due to a major intrinsic event (e.g., stroke or syncope) or overwhelming hazard [51]. An injurious fall is one that results in fractures, head injuries, sprains, bruises, scrapes, or serious joint injuries, or where the participant seeks medical care [51].

### Descriptive variables and other measures of interest

Demographic variables, medications (including chemotherapy), cancer health history, and body mass index are collected at baseline and updated throughout the study via the EHR and an in-house questionnaire. The presence of chronic health conditions is measured with the Charlson Comorbidity Index [52]. Cumulative chemotherapy doses and relative dose intensities are calculated from the EHR.

### Statistical analysis

#### Overview of modeling strategy

We will employ a *modified* growth mixture modeling (GMM) approach. GMM identifies distinct patterns of change across time that vary around different means and have unique variance and homogenous within-trajectory growth. Cases are then assigned to the “most likely class” or pattern of change over time. Changes over time are modeled as random effects and non-normal distributions and non-linear patterns of change can be modeled [53]. Typically, the growth and latent class aspects of GMMs are estimated simultaneously within a structural equation modeling (SEM) framework, although these models are much easier to estimate with time-structured data (i.e., participants are measured the same number of times at the same intervals) [54]. In the present study, measurements will not be time structured, and we will employ a modified GMM approach. With this approach, the initial growth modeling will be done with a mixed-effects model (stage 1), which flexibly handles non-time structured data, and then we will submit the intercept and growth estimates from this model to a latent class (aka latent profile) model within the SEM framework (stage 2). All analyses will be performed using R v4.2.2 [55] and Mplus v8.7 [56].

#### Handling missing data

The mixed-effects growth models will be estimated with maximum likelihood, which utilizes all available outcome data for each participant without removing participants due to missingness [57]. For the GMM stage, full-information maximum likelihood (FIML) estimation will be used to handle data that is missing completely at random (MCAR) or missing at random (MAR). For data that are MAR, variables related to the missingness will be included using the auxiliary command in Mplus (i.e., to allow unbiased parameter estimation under MAR) while not including them in the data analysis model [58]. These approaches will allow the analysis of the proposed aims in the case of patient withdrawal, maximizing statistical precision and power.

#### Confounding

We will test the influence of and include, as appropriate, all known confounders in our longitudinal and latent class models.

#### Specific analysis plan

The analysis will proceed in a series of stages.

*Hypothesis 1.1:Worsening neuropathy symptoms will be associated with concomitant worsening in functioning. *

The change over time in each symptom and functioning outcome will be modeled using a mixed-effects modeling framework implemented in the lme4 statistical package for R. The fixed and random effects structure and the shape of change across time (e.g., linear versus nonlinear) will be determined through likelihood ratio model testing and information criteria. Intercepts (initial status) and growth estimates (e.g., linear and/or quadratic trends) will be estimated for each individual patient for each outcome. All pairs of neuropathy symptom and functioning intercepts and slopes will be correlated to test Hypothesis 1.1*.*

*Hypothesis 1.2. At least two classes of patients with distinct trajectories of change in symptoms and functioning can be identified, and will be associated with significant differences in fall rates.*

 Each patient's intercept and growth estimates for each measure will be entered into a GMM to identify patient clusters with distinct symptom and function trajectory profiles. For each patient, a probability of belonging to each latent class will be assigned, and the highest membership probability will be used to make a final class assignment. Identification of the best-fitting model will be based on information criteria (e.g., Bayesian Information Criterion), where smaller numbers indicate a better fit, convergence (entropy > 0.80), the proportion of the sample in each latent class (not < 5%), posterior probabilities (mean probability of belonging in “most likely” class near 1.0), and the Lo-Mendell-Rubin adjusted likelihood ratio test (which is used to compare alternative models, e.g., k vs. k-1 classes) [53]. After a good fitting GMM model is found, the resulting latent classes will be described with respect to differences between initial CIPN symptom and functioning profile and change across time. Standard statistics (e.g., t-tests) will then be used to compare fall rates between the observed symptom and function latent classes. We will focus interpretation on effect sizes and 95% CIs. Beyond examining fall rates across the study time course, we will also explore survival models to predict time to first fall. Kaplan Meier models, Mantel-Cox log-rank tests and generalized Wilcoxon-Breslow tests will be used to evaluate differences in the distribution of time to first fall. Multivariate hazard ratios with 95% CIs and Wald χ2 statistics will be calculated from Cox models with Schoenfeld residuals used to test proportional hazards assumptions.

*Hypothesis 2.1. Sociodemographic (e.g., age, sex, comorbidities, body mass index), clinical (e.g., type of chemotherapy, # of chemotherapy cycles and/or cumulative dose of chemotherapy, disease stage, other symptoms), and mobility measures (gait and balance) can be used to predict distinct trajectories of change in neuropathy symptoms and functioning.*

 Standard statistical tests will be used to examine the association between latent class membership and sociodemographic, clinical, and mobility measures depending on level of scale (e.g., Kendall/s tau-b or Kruskal–Wallis tests). Since we will recruit both men and women into the study, we can also address sex as a biologic variable in the context of symptoms, functioning, and falls among cancer survivors**.** Thus, we will be the first to determine if sex associates with specific symptom trajectories that might lead to either gender-specific management approaches or a uniform strategy. Since there is a potentially large number of variables that will be compared we will control for false discovery rates with the Hochberg adjustment [59].

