### Study participants

The target population is adults with cancer scheduled to receive neurotoxic chemotherapy with curative intent. To be eligible to participate, participants must meet the following eligibility criteria:Age 40–85 years on the date of enrollment. We chose this age range because the side effects and symptoms from chemotherapy may differ between young, middle-aged, and advanced-aged patients, and the subsequent impact on mobility may be similarly diverse. We exclude adolescent and young adult patients (15–39 years old) who may be less vulnerable to falls and disability at a young age and adults over 85 years to limit mobility/falls associated with advanced age and multi-morbidities. The age range of patients in the study is broad enough to examine the influence of age on study outcomes.Diagnosed with stage I-III cancer, or stage IV cancer considered curable, other than cancers or metastases in the brain or spinal cord.Patients scheduled to receive neurotoxic chemotherapy, including taxane derivatives, platinum complexes, and/or vinca alkaloids.Patients without prior receipt of neurotoxic chemotherapy.Patients without cognitive difficulties that preclude answering survey questions, participating in performance tests, or giving informed consent as determined by the referring provider.Patients must be free of a medical condition, movement or neurological disorder, or medication use that contraindicates participation in mobility testing and/or confounds the ability to detect treatment-related changes in balance and mobility. Specific medical conditions include, but are not limited to, severe muscular dystrophy, severe spasticity, epilepsy, seizures, Alzheimer’s disease, and dementia; specific physical conditions include a severe balance disorder (e.g., from late-stage Parkinson’s disease or stroke), inability to ambulate (use of an assistive device is permitted), inability to stand for 3 min, or severe hearing or vision problems.

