### Outcome measures

#### Symptoms

##### Objective CIPN measures

Loss of perceived sensation is a widely accepted clinical measure to screen for CIPN [21]. We perform 3 tests of loss of perceived sensation.*Tuning fork test*: Vibratory sensation is measured by placing a 128 Hz vibrating tuning fork (US Neurologicals, LLC, Poulsbo, WA) proximal to the nail bed on the right dorsal hallux and recording the time that elapses before the participant indicates they can no longer detect vibration [22]. Three trials of the test are conducted and then averaged.*Monofilament test*: The tester records the number of times an individual detects 4 brief applications (~ 1 s) of a 10-g monofilament (Medical Monofilament, Plymouth, MA) on the sole of each foot, for a total of 8 sites [22].*Biothesiometry*: The lowest amplitude of vibration that an individual can detect, or vibration perception threshold (VPT), is assessed using a biothesiometer (Biothesiometer USA, Avon Lake, OH) [23]. A handheld device that varies vibration amplitude at a constant frequency is placed proximal to the nail bed on the right dorsal hallux. The VPT is measured by slowly increasing the amplitude from 0 V until the individual indicates that they detect vibration in their toe. Two trials are performed and averaged to generate the VPT. Biothesiometry is only performed at the final chemotherapy infusion and at all post-chemotherapy assessments.

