##### **Patient-**reported** CIPN**

Patient-reported CIPN is assessed using the Patient-Reported Outcomes version of the Common Terminology Criteria for Adverse Events v1.0 (PRO-CTCAE™: https://healthcaredelivery.cancer.gov/pro-ctcae/) reporting tool and the Functional Assessment of Cancer Therapy – Gynecologic Oncology Group Neurotoxicity 13-item questionnaire (FACT-GOG-Ntx-13) [24–27]. Two PRO-CTCAE™ items are administered weekly, asking the patient to report whether they experienced numbness or tingling in the hands or feet and how much the symptom interfered in their daily life during the last 7 days. We also administer the 13-item neuropathy subscale of the FACT-GOG-Ntx-13 which assesses the presence, severity, and interference of neuropathy symptoms in patients receiving neurotoxic chemotherapy. The scale ranges from 0–52, with lower scores indicating worse quality of life due to neuropathy. Both surveys are sent weekly for the duration of the study.

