### Sample size/power calculation

Although simulation methods are available to help estimate sample size for

GMM, this requires known values for all model parameters and is not defensible given the unknowns in this domain. With 2 symptom measures (severity and interference) and 6 function measures in our most complex GMM model, however, our n-to-items ratio meets conservative sample size recommendations for related approaches (20:1) [60] and would require 160 complete cases. To maximize statistical power we will fit parsimonious models after extensive preliminary associative analyses. Regarding class comparisons, assuming 80% power, two-sided α of 0.05, and 2 equal groups, we will be able to detect small-medium sized differences in fall rates and other continuous variables between groups (Cohen’s *d* = 0.40). For categorical variables, we will be able to detect small-medium effects (w = 0.25) for cross-tabulation tables with as many as 4 degrees of freedom. Evaluable data on 200 participants is a feasible number and will allow us to address each aim while accounting for up to ~ 20% attrition.

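### If the ordinal and bounded neuropathy measures are fitted as Gaussian in lme4, the floor or ceiling distorts individual slopes and can produce trajectory classes where none exist

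*Protocol article*

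**What the plan says.** **Model.** Under Specific analysis plan, the protocol article says that change over time in "each symptom and functioning outcome will be modeled using a mixed-effects modeling framework implemented in the lme4 statistical package". The flexibility it states concerns the fixed and random effects and the time trend: "the shape of change across time (e.g., linear versus nonlinear) will be determined through likelihood ratio model testing and information criteria". No link, response distribution, censoring or transformation is named for this stage.

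**Use of the estimates.** "Intercepts (initial status) and growth estimates (e.g., linear and/or quadratic trends) will be estimated for each individual patient for each outcome". Pairs of these estimates are correlated for Hypothesis 1.1. For Hypothesis 1.2, the Overview of modeling strategy says the analysts will "submit the intercept and growth estimates from this model to a latent class (aka latent profile) model within the SEM framework". The same overview remarks that growth mixture models can accommodate non-normal distributions. It then replaces the one-step model by this two-stage version because measurement times differ between patients.

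**Measures.** Under Patient-reported CIPN, two weekly PRO-CTCAE items ask the patient to "report whether they experienced numbness or tingling in the hands or feet and how much the symptom interfered in their daily life". The FACT-GOG-Ntx-13 runs from 0 to 52, with lower scores worse, so 52 is the no-symptom end. The monofilament count is taken "on the sole of each foot, for a total of 8 sites". The sample size section describes the largest model thus: "With 2 symptom measures (severity and interference) and 6 function measures in our most complex GMM model".

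**Patients.** Eligible patients are those "without prior receipt of neurotoxic chemotherapy", and baseline falls before the first or second cycle.

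**The concern.** The symptom measures have few levels or a hard limit, and the population is likely to begin at that limit. A Gaussian random-slope model treats a run of 'none' ratings as a flat line. Patients whose underlying state worsens without crossing the first threshold cannot be told apart from patients who do not change. Their estimated slopes pile up near one value and the remaining slopes form a long tail. A latent profile model built from normal components tends to describe such a shape with more than one component.

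The individual intercepts and slopes are the material for the Hypothesis 1.1 correlations and for the classes of Hypothesis 1.2, and Hypothesis 2.1 then predicts those classes. Hypothesis 1.2 claims that at least two classes exist, which is also what a floor tends to produce. A homogeneous population could therefore be reported as having distinct trajectories.

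**Working it through.** **Step 1. The plan's own figures.** They reproduce and are not affected by this point.
- 20 × (2 + 6) = 160 complete cases; 160 / (1 − 0.20) = 200.
- d = 0.40, 80% power, two-sided 0.05: n per group = 2(1.960 + 0.842)² / 0.40² = 98.1, so 99 per group (198 in total). Power with 100 per group is 80.7%.
- w = 0.25 with 4 degrees of freedom and N = 200: power 82.0%.

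**Step 2. Inputs to the simulations.**
- From the article: n = 200; weekly ratings; 0-52 score; 25-90% developing CIPN (Introduction); 2 symptom and 6 function measures; BIC, entropy above 0.80 and no class below 5%.
- Assumed: five response levels and 70-95% at 'none' at baseline (the range used differs by check and is given where it matters). The article gives neither.
- Population: one normal distribution of latent intercepts and slopes, with no classes.

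Each data set was fitted with a Gaussian random intercept and slope model. The individual estimates then went into a normal latent profile model with equal covariance across classes, either diagonal or full. 'Uncut' means the same latent data without rounding to levels or limits.

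**Step 3. One measure, 17 weekly ratings, 95% at 'none' at baseline, 1-3 classes, 40 runs per setting.** Paired figures are diagonal / full covariance. 'All three' means that the BIC-best model also met entropy and class share.

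| Symptomatic at end | Data | 2+ classes by BIC | All three | Slope correlation, estimated vs true |
|---|---|---|---|---|
| 25% | uncut | 10% / 0% | 0% / 0% | 0.88 |
| 25% | five-level | 100% / 100% | 30% / 40% | 0.53 |
| 25% | 0-52 | 100% / 100% | 38% / 17% | 0.48 |
| 60% | uncut | 10% / 0% | 0% / 0% | 0.88 |
| 60% | five-level | 100% / 100% | 70% / 53% | 0.58 |
| 60% | 0-52 | 100% / 100% | 70% / 50% | 0.54 |
| 90% | uncut | 15% / 0% | 3% / 0% | 0.88 |
| 90% | five-level | 100% / 100% | 57% / 65% | 0.63 |
| 90% | 0-52 | 100% / 95% | 80% / 33% | 0.60 |

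A separate simulation (full covariance, 80-95% at 'none', 25-90% symptomatic at the end) gave 100% by BIC against 0-4% uncut. All three criteria were met in 28-84%, and the slope correlation was 0.61-0.82 against 0.92.

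**Step 4. The plan's eight-measure layout, 20 runs per setting.** Two five-level symptoms and six continuous functions were compared with eight continuous measures.
- Independent measures, three settings (80% or 95% at 'none', 25% or 60% symptomatic at end): two or more classes by BIC in 95-100% (diagonal) and 90-100% (full), against 5% and 0%. All three criteria were met in 60-100%, against 0-5%.
- Correlated measures: the diagonal model found two or more classes in 100% even with all measures continuous. The full model did so in 100% with the ordinal items and 0% without.

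**Step 5. Recovery phase and the other selection criteria.** Layout: 70 weeks, a rise over 18 weeks and then partial recovery, linear and quadratic growth, full covariance, 80-90% at 'none', 30-85% symptomatic at end of treatment, 30 runs per setting.
- Five-level item: BIC chose two classes in 100%, all three criteria were met in 97-100%, and mean posterior probability was 0.96-0.99.
- The two-against-one likelihood ratio (median 64-151) exceeded its simulated null 95th percentile (9.5 or 13.2) in 100%. This stands in for the Lo-Mendell-Rubin test, which was not itself run.
- Uncut data: BIC chose two classes in 0%.

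**Step 6. Hypothesis 1.1.** With a five-level item over 70 weeks and 70-95% at 'none' (nine settings, 150 runs each), a symptom-function slope correlation of about −0.47 became −0.27 to −0.43. As ratios, 0.27 / 0.47 = 0.57 and 0.43 / 0.47 = 0.91, a loss of about 9% to 43%.

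**Step 7. Does an ordinal first stage cure it?** Ordinal estimates computed with the true parameters raised the slope correlation to 0.72-0.87, from 0.61-0.82. They still gave two or more classes by BIC in 76-100% of runs in 5 of 6 settings. A smaller check (three settings, 12 runs each) gave 0-17%. Its worst case is 2 of 12, with an exact 95% interval of about 2% to 48%. One reason is plain: patients who always answer 'none' at the same times share one posterior mean whatever the link, so a point mass remains in the input to stage 2.

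**The case against.** **Gaussian is inferred.** The article names a framework and a package, no distribution. lme4 also fits binomial and count models, and Mplus is named beside R. A condensed article may leave the response model for each outcome to a fuller document. This stands, and the point is therefore conditional. It does not dispose of the matter: the text assigns every symptom outcome to one package that has no cumulative-link model, and the stated flexibility does not touch the response scale.

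**The floor is assumed.** Eligibility excludes prior neurotoxic chemotherapy, not neuropathy from other causes. Ages run to 85, and baseline may follow one infusion. This also stands, hence the range of baseline shares.

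**Severity and interference may not be the PRO-CTCAE items.** The article also describes the FACT-GOG-Ntx-13 in terms of presence, severity and interference. The identification is an inference, but the 0-52 score shows the same effect.

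**Stronger readings that a reader might infer.**
- That lme4 cannot handle the monofilament count. It can, with a binomial family.
- That the floor is the only source of spurious classes. With correlated measures, which Hypothesis 1.1 expects, a diagonal profile model produces them from continuous data too. Only the full-covariance comparison isolates the floor.
- That any classes found must be artefacts. The article expects CIPN in 25-90% of patients, so groups with and without symptoms may be real; a single latent population is the simulation's premise.
- That timed tests and sway need a log scale. No defect was shown for them.

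**Conclusion.** The point holds in conditional form. If the numbness/tingling items and the 0-52 score are fitted as Gaussian, and most patients start at the no-symptom end, three things follow.
- Individual slopes are recovered less well (0.48-0.82, against 0.88-0.92 uncut, in the simulations of Step 3).
- The Hypothesis 1.1 correlations shrink.
- Two or more classes can meet the BIC, entropy and class-share criteria in a population with none. The rate is 17-84% for a single measure in Step 3 and 60-100% in the eight-measure layout with independent measures.

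Finding two classes would then not by itself support Hypothesis 1.2. The size depends on the assumed five levels and baseline share. Continuous measures such as TUG time and grip strength are not subject to the floor, and the sample-size arithmetic stands. A reader might infer that changing to an ordinal model settles the matter. Step 7 does not support that: it improves the slopes but does not reliably remove the spurious classes. The plan should be changed on this point, and no new data are required.

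**What to change.** **Hypothesis 1.1.** State the response model for each outcome type:
- a cumulative-link mixed model for the PRO-CTCAE items (R package ordinal, or Mplus);
- a censored or two-part model for the 0-52 score;
- a binomial mixed model with 8 trials for the monofilament count, available in lme4.

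**Hypothesis 1.2.** Do not rely on carrying individual point estimates forward. Choose one of two routes:
- fit the mixture in one step in Mplus, which the plan already names, with categorical or censored outcomes and individual measurement times; or
- keep two stages, simulate data sets from the fitted one-class ordinal model at the observed measurement times, pass them through the same procedure, and claim two or more classes only if the observed improvement in fit exceeds what the one-class data produce.

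**Cost.** Analysis wording, possibly one R package, and longer run time. Latent-scale slopes need translating for readers, for example into the predicted probability of reporting a symptom at a given week.

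### Hypothesis 1.1 and the class comparisons treat estimated slopes and assigned classes as known, which biases the correlations and mildly to moderately dilutes the class contrasts

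*Protocol article*

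**What the plan says.** The Protocol article describes two linked stages.

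- **Stage 1 (Specific analysis plan, Hypothesis 1.1).** Each symptom and functioning outcome has its own lme4 model. "Intercepts (initial status) and growth estimates (e.g., linear and/or quadratic trends) will be estimated for each individual patient for each outcome". The test of Hypothesis 1.1 follows at once: "All pairs of neuropathy symptom and functioning intercepts and slopes will be correlated to test Hypothesis 1.1".
- **Stage 2 (Overview of modeling strategy).** "we will submit the intercept and growth estimates from this model to a latent class (aka latent profile) model". The reason given for two stages is that patients are not measured on a common schedule.
- **Class comparison (Specific analysis plan, Hypothesis 1.2).** For each patient, "the highest membership probability will be used to make a final class assignment". Standard tests such as t-tests then "compare fall rates between the observed symptom and function latent classes". Predictors are compared across the same classes under Hypothesis 2.1. Model choice uses BIC, entropy above 0.80, at least 5% of the sample per class, mean posterior probability near 1.0 and the Lo-Mendell-Rubin test.
- **Missing data (Handling missing data).** Stage 1 uses maximum likelihood on all available outcome data. "For the GMM stage, full-information maximum likelihood (FIML) estimation will be used to handle data that is missing completely at random" or at random, with auxiliary variables entered in Mplus.

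No stated step carries forward the error in the stage-1 estimates or in the class assignment.

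**The concern.** A patient's predicted slope is not the true slope. Correlating predictions from separate models therefore does not estimate the correlation between true changes, which is what Hypothesis 1.1 is about. The bias has no fixed direction:

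- Slope-slope correlations are pulled toward zero by estimation error.
- Intercept-slope pairs can pick up a correlation that is not there, because a predicted slope partly reflects the same outcome's intercept.
- Two tests done at the same visit share that day's error, which can pass into the slope correlation.

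A significant result therefore cannot be defended as conservative, and a weak one may understate a real link.

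Placing each patient in the most probable class mixes some members of one class into the other. Differences in falls and predictors between the assigned classes are then smaller than between the true classes. This affects Hypotheses 1.2 and 2.1.

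**Working it through.** **The plan's own figures.** For d = 0.40, two-sided alpha 0.05 and 80% power, n per group = 2 × (1.96 + 0.84)² / 0.40² ≈ 98.1, so 99. With 100 per group, power is 0.804 (noncentral t). Also 20 × 8 = 160 and 160 / 0.80 = 200. The stated figures reproduce at N = 200.

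**Inputs.** From the article: weekly symptom surveys; clinic tests every 4–6 weeks during chemotherapy, then at 3, 6, 9 and 12 months; entropy floor 0.80. Assumed, because the article does not give them: about nine clinic visits, residual variance, slope variance and same-visit residual correlation.

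**Hypothesis 1.1, approximate formula.** With slope reliabilities L1 and L2, true slope correlation ρ and residual correlation re, on a common visit schedule:

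r = ρ√(L1·L2) + re√((1−L1)(1−L2))

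- L1 = L2 = 0.5, ρ = 0.50, re = 0: r = 0.50 × 0.5 = 0.25.
- √(L1·L2) = 0.4 gives 0.20; √(L1·L2) = 0.8 gives 0.40.

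**Mixed-model predictions** (true slope-slope and intercept-intercept correlations 0.50):

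- Residual variance equal to intercept variance: slope-slope appears as 0.20–0.35 with nine visits on both outcomes, and 0.26–0.40 with weekly symptoms against nine visits. At slope SD equal to intercept SD, the values are 0.27–0.29 and 0.34–0.35.
- With half that slope SD, and residual variance 0.5–1.0 of intercept variance, the values fall to 0.09–0.26.
- An intercept-slope pair with true value 0 appears as 0.11–0.17 when an outcome's own intercept and slope are uncorrelated. If that correlation is −0.3, the range is about −0.07 to 0.10.
- Models fitted to 25 simulated studies (200 patients, up to nine visits, 20% withdrawing, residual variance equal to intercept variance) gave mean slope-slope 0.26 (true 0.50), intercept-intercept 0.41 (true 0.50) and intercept-slope 0.13 (true 0).

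**Shared visit error.** With no true slope link and a same-visit residual correlation of 0.3, two outcomes at nine common visits show 0.10–0.25. The rejection rate is about 29–95% against a nominal 5% at N = 200. For a weekly survey against a clinic test the false correlation is at most about 0.08.

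**Class assignment.** I used a two-class normal mixture tuned to entropy 0.80. The dilution factor is PPV + NPV − 1, where PPV and NPV are the shares correctly assigned to the smaller and larger class. A true rate ratio of 2 is seen as (2·PPV + 1 − PPV) / (2(1 − NPV) + NPV).

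| Smaller class | PPV | NPV | Factor | Rate ratio seen |
|---|---|---|---|---|
| 50% | 0.945 | 0.945 | 0.89 | 1.945 / 1.055 = 1.84 |
| 20% | 0.885 | 0.960 | 0.845 | 1.885 / 1.040 = 1.81 |
| 10% | 0.80 | 0.959 | 0.76 | 1.80 / 1.041 = 1.73 |

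For equal classes, d = 0.40 × 0.89 ≈ 0.356, and power at N = 200 falls from 80% to about 70%. At entropy 0.90, d is about 0.378 and power 76%. For a 10% class at entropy 0.80, d is about 0.30 and power falls from 39% to 21%.

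**Missing data.** In the simulated studies with 20% withdrawal, no stage-2 input was missing, since any patient with one observation on a measure receives an intercept and slope.

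**The case against.** **Selection rules limit the class dilution.** This stands in part. A reader might infer that a class at the 5% floor would be badly contaminated, with a rate ratio of 2 seen as about 1.59. The plan would not accept that solution: at entropy 0.80, modal assignment places only about 3 of 200 patients in such a class, which fails the 5% rule. The 10% case is borderline on BIC, and its PPV of 0.80 would fail the posterior-probability rule if that is read class by class, which the text does not say. Entropy also takes the stage-1 estimates as known, so it does not reflect their error.

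**False positives depend on invented inputs.** This also stands in part. A reader might infer that Hypothesis 1.1 is likely to be confirmed with no true link. With reliability 0.5 and residual correlation 0.4, r = 0.20 and 72% of studies at n = 160 would reject. Neither input is in the article, and the mechanism needs two tests at one visit. Patient-reported neuropathy comes from weekly home surveys, and the devices are worn on the days after the visit. The risk is confined to pairs such as a sensation test against a performance test.

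**Shrinkage cannot change a correlation.** Uniform shrinkage indeed cannot. The cause is estimation error, and separate least-squares fits per patient would attenuate too.

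**The missing-data plan is sound.** Largely so. A reader might infer that protection is absent where data are missing. Stage-1 maximum likelihood is valid under MAR given the observed outcomes. Stage-2 FIML also has a use: biothesiometry starts only at the final infusion, so earlier withdrawers have no value, and some patients may never wear the devices.

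**Two stages are needed, and interpretation rests on effect sizes.** Irregular timing does not prevent a bivariate mixed model, and the effect sizes are themselves what is biased.

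**Conclusion.** The point holds, and the analysis should be changed before it is run. The only stated test of Hypothesis 1.1 is biased. A true slope-slope correlation of 0.50 would be seen as about 0.20–0.40, and lower if slopes vary little between patients. A null intercept-slope pair would be seen as about 0.11–0.17. These figures assume residual variance equal to intercept variance and about nine clinic visits, and the intercept-slope figure also assumes that an outcome's own intercept and slope are uncorrelated. Spurious slope correlation is a concern only for pairs of same-visit clinic tests.

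The class dilution is mild to moderate, with a factor of about 0.89 for equal classes at the entropy floor and 0.76 for a 10% class. It assumes a two-class normal mixture.

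On missing data only a narrow point remains: auxiliary variables at stage 2 act only for patients with no data at all on a measure. The documents do not support a claim that missing data are unprotected.

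**What to change.** **Hypothesis 1.1.** For each symptom-function pair, fit a bivariate mixed model with correlated random intercepts and slopes across the two outcomes. For measures taken at the same visit, add correlated residuals. Test the random-effect correlation directly and report it with its interval. The model uses each patient's actual measurement times.

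**Hypotheses 1.2 and 2.1.** Keep the latent class model, but compare falls and predictors across classes with a bias-adjusted three-step method (BCH or ML, available in Mplus) in place of standard tests on modal classes. This corrects for classification error, not for error in the stage-1 estimates that form the classes; say so as a limitation.

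**Missing data.** State that protection rests mainly on stage-1 maximum likelihood under MAR, and that the stage-2 auxiliary variables serve patients with no data on a measure. I do not suggest entering missingness variables as stage-1 covariates. The article keeps them out of the analysis model on purpose, and slopes adjusted for variables such as age or comorbidity would lose part of what Hypothesis 2.1 examines.

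**Cost.** Changed analysis wording and more programming; no change to data collection. Some bivariate models may not converge without simplified random effects, so fix the order of simplification in advance.
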